## UNIVERSITY SELF-ASSESSMENT CHECKLIST

|                                                                                                                                                                                                       | Yes                                 | No                                  | Don't know               |
|-------------------------------------------------------------------------------------------------------------------------------------------------------------------------------------------------------|-------------------------------------|-------------------------------------|--------------------------|
| 1. Does the study avoid obtaining an informed consent of participants?                                                                                                                                |  |             |  |
| 2. Will the study collect and use data that is not anonymized (e.g., name, video or audio recordings from participants)                                                                   |  |             |  |
| 3. Will the study involve vulnerable individuals or groups who cannot themselves provide informed consent (e.g. children, people with learning disabilities, clinical populations)?                   |             |  |  |
| 4. Does the study involve participants that are uninformed about their participation in the study?                                                                                                    |  |             |  |
| 5. Are the participants asked to provide intimate, sensitive or distressing information (e.g. about illegal or deviant behavior, sexual orientation, traumatic experiences)?                          |             |  |  |
| 6. Could the study negatively affect participant's physical integrity (e.g., taking medications or alcohol, taking blood, physical strain through physical exertion)?                                 |             |  |  |
| 7. Could the study negatively affect participant's psychological integrity (e.g., triggering mental stress, severe emotions, pain or other negative effects that go beyond an everyday level)?        |             |  |  |
| 8. Is there a substantial dependency relationship between the participants and any of the involved researchers?                                                                                       |             |  |  |
| 9. Will the participants be intentionally deceived or misled by the researcher (e.g., by manipulated performance feedback, by providing false information about the objectives of the investigation)? |             |  |  |
| 10. Does the study involve coercive financial or non-financial incentives (i.e., incentives that can threaten the voluntary choice to participate in the study)?                                      |             |  |  |
| 11. Is the purpose of the study to significantly influence participant's life (e.g., influencing people's voting behavior, people's job search behavior or outcomes)?                                 |  |             |  |
| 12. Does any member of the research team have any association that poses or could be perceived as posing a conflict of interest in connection with the results of the study?                          |             |  |  |

A) No informed consent (checklist #1 and #4)

The letter to the adult citizens of the city of Ravensburg states: *"The vaccination campaign is scientifically monitored"*. Furthermore, the treatment group is informed in the letter that they were selected "randomly" according to the randomization. However, the population is not informed in detail that they are taking part in a field experiment. The advantage of this approach is that the external validity of the results is higher than in a laboratory experiment, for example, as it is a real situation with a real vaccination schedule (Harrison and List 2004). Providing information about the field experiment in advance would make the field experiment design impossible or distort the results. Since all letters contain information about the COVID-19 vaccination or the vaccination dates, the interest in knowledge clearly outweighs the interest in information in advance from a research perspective. A detailed explanation of accompanying research could lead to already hesitant/vaccine-skeptical people being further deterred. The Hawthorne effect is particularly worrying in this context, because it is acceptable that a reference to accompanying research could already influence vaccination behavior if a feeling of scientific observation arises. In the popular debate, it is not uncommon for people to argue against vaccination on the grounds that they are being used as test subjects. It is precisely this feeling that must be avoided in the context of vaccination.

For this research project, we are guided by medical standards and the procedure described in the relevant literature (Benjamin-Chung et al. 2018). Recent publications also show that this approach is internationally recognized and practiced in the scientific community (Campos-Mercade Pol et al. 2021; Chang et al. 2021).

*Furthermore, the principle of informed consent is usually sufficiently taken into account if the research project is carried out by public institutions (in this case the city of Ravensburg) and their consent has been obtained. The project is intended to examine or test a public benefit or service program (here: the effects of the vaccination campaign). The population contacted by the city will not be deceived and will receive all information on opportunities and risks. In particular, before the vaccination, the usual information is provided by the medical staff and a written consent to the vaccination is given. The city of Ravensburg will report publicly on the study once it has been completed and the research team has evaluated the results.*

---

 Poverty Action Lab [https://www.povertyactionlab.org/sites/default/files/research-resources/rr\\_irb\\_annotated-informed-consent-checklist\\_0.pdf](https://www.povertyactionlab.org/sites/default/files/research-resources/rr_irb_annotated-informed-consent-checklist_0.pdf), p. 4 f., accessed on 28.10.2021.

The field experiment will not expose the adult citizens of the city of Ravensburg to any additional burden or stress; rather, they will receive the necessary information on vaccination or vaccination dates and may have less research effort than third parties dealing with the vaccination decision. They would be exposed to these letters even if the experiment had not been carried out, as the city of Ravensburg is planning to send such a letter anyway. The experimental character results solely from the randomization of a monetary incentive, which does not result in any disadvantages for the participants. Randomizing monetary incentives is a comparatively fairer option than awarding such incentives on a "first come, first served" basis, for example, which would favor people with more resources. The letters can also be ignored without consequences and the website links do not have to be visited. There is therefore no or only a minor impairment or restriction. It is not a form of deception, as there is a real possibility for all groups to attend a vaccination appointment. The population will be informed by the city of Ravensburg after the study that this is a scientifically supported procedure and that there were addressee groups with different letters.

#### B) Personal data (Checklist #2)

For the field experiment, personal data is used for the purposes of contacting and measuring the effects, which the city of Ravensburg collects after its own data protection review and may make available for research purposes. For research purposes, the data will be pseudonymized or anonymized as far and as soon as possible, especially for the evaluation after the cover letter.

#### C) Influence on individual life (Checklist #11)

A vaccination can be described as having a significant influence on individual life. From a scientific point of view, in the vast majority of cases this is a very positive influence on individual and public welfare. Incidentally, the people taking part agree to the vaccination of their own free will and receive the medical information required by law before being vaccinated.

In this context, it should be emphasized that this field experiment is about the vaccination itself. The city of Ravensburg would carry out a corresponding information campaign to increase the vaccination rate with incentives anyway, even if there was no cooperation within the framework of a field experiment. In addition, the official information website linked in the letter presents the potential risks of vaccination according to the official information from the Federal Ministry of Health, in comparison to the risks of a COVID-19 infection.

As confirmed in relevant published articles (Brewer et al. 2017; Lunn et al. 2020), from a research perspective, the interest in measures to increase the vaccination rate

outweighs the conceivable adverse effects on individuals due to incentives or information letters (Patel 2021). As stated at the beginning, the American Psychological Association emphasizes the importance of field studies and field experiments during COVID-19 vaccination efforts: "Interventions need to be tested in a real-world context."

. There is also considerable public interest in the knowledge gained from this study.

## TRIAL PROTOCOL

Draft, to be pre-registered on Open Science Framework

### Hypotheses

H1-1 (direct or "total" effect #1): Offering a set of monetary incentives increases the number of unique website visits (on a municipal webpage with information on COVID-19 vaccination) among treated subjects in treatment clusters compared to equivalent subjects in control clusters (i.e., in each control cluster, the person who would have received the treatment letter had they been assigned to a treatment cluster). H1-2 (direct or "total" effect #2): Offering a set of monetary incentives increases COVID-19 vaccinations (tracked at seven city vaccinations events) among treated subjects in treatment clusters compared to equivalent subjects in control clusters (i.e., in each control cluster, the person who would have received the treatment letter had they been assigned to a treatment cluster). H2 (spillover effect): Offering a set of monetary incentives increases COVID-19 vaccinations among untreated individuals in treatment clusters compared to untreated subjects in control clusters (minus the individual who would have received a treatment letter in the control cluster if they were assigned to a treatment cluster). H3-1 (overall effect #1): Offering a set of monetary incentives increases unique website visits among treated and untreated individuals in treatment clusters compared to untreated subjects in control clusters. H3-2 (overall effect #2): Offering a set of monetary incentives increases COVID-19 vaccinations among treated and untreated individuals in treatment

### Design Plan

Study type

Experiment

Blinding

No blinding is involved in this study.

Study design

The design is a blocked, two-stage (individual and household) randomized controlled field experiment.

Randomization

The study will be conducted in a medium-sized city in Germany. Treatment assignment follows a two-stage randomization process. In the first stage, all housing addresses within the city will be randomized into two groups (i.e., intervention group and control group), blocked by household size. In the second stage, one resident of each address in both groups will be randomly selected (a "cluster representative"). The cluster

representatives in the intervention group only will be sent the intervention letter. All remaining residents will be sent the control letter. The randomization will be conducted in R (version 4.1.1) using the function “sample” with the seed set to 2021.

### **Sampling Plan**

Existing Data

Registration prior to creation of data

Data collection procedures

The study will be conducted in the city of Ravensburg, Germany. All residents of the city (age 18 and older) will be subject to the trial (as per official residency records). The only notable exception is that the study excludes the inmates of a local prison (n=257) and the second largest cluster of the city (n=75). Treatment assignment follows a two-stage randomization process. In the first stage, all housing addresses within the city will be randomized into two groups (i.e., intervention group and control group), blocked by household size. In the second stage, one resident of each address in both groups will be randomly selected (a “cluster representative”). The cluster representatives in the intervention group only will be sent the intervention letter. All remaining residents will be sent the control letter. The treatment group will receive a letter from the mayor of the city inviting them to get a COVID-19 vaccination at one of seven public vaccination events. The letter offers two financial incentives. If the recipient is not already vaccinated and gets vaccinated at the vaccination events, they will receive 20 Euros (in the form of a shopping voucher). Additionally, another 20 Euro incentive is offered if more than 900 city residents get vaccinated at one of the seven vaccination events. If the recipient is already vaccinated, they can still get the second incentive if they give the treatment letter to someone else and that individual brings it to one of the seven vaccination events, gets vaccinated, and more than 900 city residents get vaccinated during the one of the seven vaccination events. The control group will get the same letter as the treatment group but without the offer of monetary incentives.

Sample size

The sample consists of all residents of the city (n = 41,549) clustered into 10,033 addresses. The only notable exception is that the study excludes the inmates of a local prison (n=257) and the second largest cluster of the city (n = 75).

Sample size rationale

The sample size is determined by the population of the city. Based on simulation-based power calculations, we are able to detect a minimal direct or “total” effect of 2.6 percentage points, a spillover effect of 1.5 percentage points, and an overall effect of 1.3 percentage points with approximately 80% statistical power (alpha = 0.05). This

calculation is based on the assumption that 20% of the population of the city is not eligible for a primary vaccine or booster and that eligibility is uniformly distributed across individuals. We project that up to 20% of the control group will get vaccinated at these events. The code for the power calculation is attached under "data collection procedures".

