### **Analysis Plan**

#### Statistical models

We will use OLS regression with a treatment indicator, block fixed effects, and control covariates (consisting of a binary indicator for female, an indicator for non-German nationality, age, and age squared) in all subsequent analyses unless indicated otherwise. To ensure robustness, a secondary analysis will regress outcomes against the treatment indicator without controls. H1-1 (direct or “total” effect #1): Information uptake regressed against treatment group for only cluster representatives, with robust standard errors. H1-2 (direct or “total” effect #2): Vaccination uptake regressed against treatment group for only cluster representatives, with robust standard errors. H2 (spillover effect): Vaccination uptake regressed against treatment group for all individuals who are not cluster-representatives, with robust clustered standard errors. H3-1 (overall effect #1): Information uptake regressed against treatment group for all individuals, with robust clustered standard errors. H3-2 (overall effect #2): Vaccination uptake regressed against treatment group for all individuals, with robust clustered standard errors.

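### The detectable spillover (1.5 pp) and overall (1.3 pp) effects contain almost no allowance for correlation within addresses, so at the planning uptake of 20% their power falls below 80% once that correlation is material

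*Protocol*

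**What the plan says.** The Sampling Plan states that "The sample consists of all residents of the city (n = 41,549) clustered into 10,033 addresses". Under Sample size rationale it reports simulation-based power: "we are able to detect a minimal direct or “total” effect of 2.6 percentage points", and then "a spillover effect of 1.5 percentage points, and an overall effect of 1.3 percentage points with approximately 80% statistical power", at alpha 0.05. The listed assumptions are that 20% of the population is not eligible, "that eligibility is uniformly distributed across individuals", and that up to 20% of the control group will be vaccinated at the events. No correlation between residents of one address is mentioned.

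The Design Plan makes the address the first-stage unit of randomisation, blocked by household size. Under Statistical models, the direct effect (H1-2) is estimated in cluster representatives only, one per address, with robust standard errors. The spillover effect (H2) uses everyone else with clustered standard errors. The overall effect (H3-2) is "Vaccination uptake regressed against treatment group for all individuals, with robust clustered standard errors".

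**The concern.** When whole addresses are randomised and co-residents resemble each other, the effective sample for H2 and H3-2 is smaller than the head count. The clustered standard errors will reflect this in the analysis, so the power calculation should reflect it too. The three stated figures instead shrink almost exactly with the square root of the number of individuals, as they would if residents were independent.

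That sits badly with the rest of the protocol. The background section expects pronounced network effects within address clusters, and the exploratory analysis section treats everyone at one address as one social network. Eligibility is also spread evenly over individuals, although earlier vaccination may well be shared within a home.

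What is at stake is how informative the trial is expected to be on spillover, which the protocol names as its research gap.

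**Working it through.** **Inputs.** From the Sampling Plan: 41,549 residents, 10,033 addresses, 80% eligible, control uptake up to 20%, detectable effects 2.6 / 1.5 / 1.3 pp, power about 80%, alpha 0.05. Derived: non-representatives 41,549 − 10,033 = 31,516; mean address size 41,549 / 10,033 = 4.14; mean non-representatives per address 31,516 / 10,033 = 3.14. Allocation is 1:1. Sidedness is not stated; two-sided is used because it reproduces the figures (one-sided power would be 87% to 90%).

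**Step 1: reproduce the plan's figures with independent residents.** Take uptake of 20% and the effect e among the eligible 80%, and analyse all residents: p0 = 0.8 × 0.20 = 0.16, p1 = 0.8 × (0.20 + e), SE = √{[p0(1−p0) + p1(1−p1)] / n per arm}, power = Φ(|p1−p0|/SE − 1.96).

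| Effect | n per arm | p1 | SE | Difference / SE | Power | Detectable at 80% |
|---|---|---|---|---|---|---|
| Direct, 2.6 pp | 5,016.5 | 0.1808 | 0.00750 | 2.77 | 79% | 2.63 pp |
| Spillover, 1.5 pp | 15,758 | 0.1720 | 0.00419 | 2.86 | 82% | 1.47 pp |
| Overall, 1.3 pp | 20,774.5 | 0.1704 | 0.00364 | 2.85 | 81% | 1.28 pp |

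The detectable effects round to 2.6, 1.5 and 1.3. Independence therefore reproduces all three stated values.

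**Step 2: the design effect implied by the stated figures.** The direct analysis has one person per address, so it fixes the variance without clustering. To a close approximation, dividing by it cancels uptake, eligibility, alpha and power: implied DEFF = (MDE / 2.6)² × n / 10,033.

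- Spillover: (1.5/2.6)² × 31,516/10,033 = 1.046.
- Overall: (1.3/2.6)² × 41,549/10,033 = 1.035.
- With every figure rounded in the plan's favour, (1.55/2.55)² × 31,516/10,033 and (1.35/2.55)² × 41,549/10,033 both give 1.16.

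For equal address sizes DEFF = 1 + (m − 1) × ICC. The implied ICC is 0.046/2.14 = 0.02 (spillover) and 0.035/3.14 = 0.01 (overall). At the rounding limit it is 0.16/2.14 = 0.075 and 0.16/3.14 = 0.05. Unequal sizes would make these smaller.

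**Step 3: power with clustering, at 20% uptake.** Divide n by DEFF. The ICC of the outcome is an assumption. Equal sizes (m = 3.14 and 4.14) are the most favourable case.

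| Assumed ICC | DEFF spillover / overall | Power at 1.5 pp / 1.3 pp | Detectable, pp |
|---|---|---|---|
| 0.02 | 1.04 / 1.06 | 80% / 79% | 1.50 / 1.32 |
| 0.05 | 1.11 / 1.16 | 78% / 76% | 1.55 / 1.37 |
| 0.10 | 1.21 / 1.31 | 74% / 70% | 1.62 / 1.46 |
| 0.20 | 1.43 / 1.63 | 67% / 61% | 1.76 / 1.63 |
| 0.30 | 1.64 / 1.94 | 61% / 54% | 1.89 / 1.79 |

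**Step 4: unequal sizes.** The second largest cluster, which is excluded, had 75 adults, so sizes clearly vary. Replacing m by m(1 + CV²), with an assumed CV of 1 and ICC 0.10, gives DEFF 1.53 / 1.73 and power 64% / 58%. A simulation with correlated uptake, an assumed skewed size distribution and cluster-robust errors (600 runs) gave 66% / 64% at ICC 0.10.

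**Step 5: lower uptake.** Repeating Steps 3 and 4 with 10% uptake among the eligible:

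| Assumed ICC | Equal sizes, power at 1.5 / 1.3 pp | Size CV 1, power at 1.5 / 1.3 pp |
|---|---|---|
| 0.10 | 93% / 91% | 87% / 82% |
| 0.20 | 89% / 85% | 76% / 68% |
| 0.30 | 84% / 78% | 66% / 57% |

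**The case against.** The strongest reply is that 20% is a ceiling. Below 50% uptake the variance rises with uptake, so the ceiling is also the least favourable planning value. Step 5 shows that at 10% uptake with equal sizes, power stays at or near 80% even at ICC 0.30. Lower uptake is plausible: the bonus threshold of 900 vaccinations is 900/41,549 = 2.2% of residents, whereas 16% of residents would be about 6,650. The threshold is not a forecast, but the point stands. A reader might infer that the design cannot deliver 80% power at 1.5 and 1.3 pp; the documents do not support that without the condition on uptake. Low uptake does not make the three figures consistent with each other, however. At 10% the direct analysis could detect about 1.98 pp, so 2.6 pp would be too pessimistic while the other two still left out clustering.

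Second, a reader might infer that the figures hold only under strict independence. That is too strong: an ICC of 0.01 to 0.02 fits them, and up to 0.05 to 0.075 fits with favourable rounding and equal sizes. The power code is said to be attached but is not in the text, so its dependence structure is inferred from the ratios.

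Third, the ICC and the size CV are assumptions. An address can be a building with several households, and the protocol itself uses shared last name plus address as a narrower network. A high common ICC across large buildings may therefore be too severe. Covariates and block effects may also recover some precision, though the protocol quantifies none.

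Fourth, nothing in the protocol says that a null result will be read as excluding 1.5 pp. What a null result excludes will come from the estimate and its clustered standard error, which are already planned.

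**Conclusion.** The point holds in a conditional form. The stated 1.5 and 1.3 pp carry design effects of about 1.05 and 1.04, at most 1.16, which is next to no allowance for the clustering that the design creates and the analysis will charge for. This follows from the protocol's own figures and needs no assumed ICC. The size of the loss does need one. At 20% uptake among the eligible and equal address sizes, power at the stated effects drops by a few points at ICC 0.05 and to 61% (spillover) and 54% (overall) at ICC 0.30, and further with unequal sizes. At clearly lower uptake much or all of the loss may disappear.

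The sample is the whole city, and the estimates, type I error and intervals are unaffected. What is wrong is two stated planning figures. They should be corrected; they do not put the trial's conclusions at risk.

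**What to change.** Rerun the existing power simulation with:

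- the actual address sizes from the register;
- eligibility and uptake correlated within address, over a stated ICC range such as 0.02 to 0.30;
- the planned model with clustered standard errors, and with block effects and covariates if credit is taken for them;
- control uptake at 20% and at lower values such as 10% and 5%.

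Replace the 1.5 and 1.3 pp figures with the resulting detectable effects, and state the ICC, the uptake and the sidedness of the test beside them. Keep 2.6 pp for the direct effect at 20% uptake.

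The cost is rerunning code that already exists and publishing two figures that, at 20% uptake, will be less favourable. The sample, the randomisation and the analysis model do not change.
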